### Treatments for MDD in adolescence

The United Kingdom (UK) National Institute for Health and Care Excellence (NICE) guidelines recommend a stepped-care approach for patients with MDD, where treatment options advance alongside escalating need for care. Although not always successful in leading to remission, provision of treatment, either in the form of psychotherapy, pharmacotherapy, or both, often is essential in order to interrupt the cycle of episodic relapse and recurrence in MDD. In adolescents with MDD, a form of psychotherapy such as cognitive behavioral therapy (CBT) is first provided which may or may not be accompanied by pharmacotherapy treatment with selective serotonergic reuptake inhibitors (SSRIs) such as fluoxetine (20 mg-60 mg).

A pragmatic randomised controlled superiority trial by our group compared SSRI and specialist clinical care (SCC) with a combined treatment regime of SCC + SSRI + CBT and showed that the addition of CBT was no more effective than SCC + SSRI at effecting remission by 28 weeks of treatment [13]. Although that study did not have a CBT-only or non-treatment control group, March and colleagues [14] noted that CBT alone was not superior to placebo in effecting remission by 12 weeks and both were less effective than fluoxetine alone or combination therapy.

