## Methods/Design

### Study overview

MR-IMPACT is a pragmatic effectiveness trial of depression in adolescence. All adolescents enrolled in MR-IMPACT are simultaneously taking part in the Improving Mood with Psychoanalytic and Cognitive Therapies (IMPACT) trial [30], and have been randomly allocated to one of three forms of talking therapy (short-term psychoanalytic psychotherapy [STPP], SCC, and CBT; Figure 1). The IMPACT recruitment, baseline assessment and randomization procedures can be found together with the treatment protocol for each therapeutic arm in Goodyer et al. [30]. Another adjunct study of IMPACT, IMPACT-genes and hormones, will collect salivary cortisol pre- and post-therapy to assess HPA-axis functioning [30]. In adherence to UK NICE guidelines, patients allocated to any treatment arm may also be prescribed up to 50 mg of Fluoxetine for symptom reduction in the presenting episode.

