### Follow-up assessment

Patients who were randomized to the CBT arm of the IMPACT clinical trial who have completed a minimum of 6 out of a maximum of 20 offered CBT therapy sessions will be invited back for a second MRI visit approximately 24 weeks following their first therapy appointment. All healthy comparison participants will be invited back for a second MRI visit at least 24 weeks from their first scan date to ensure a comparable length of time has passed between scans across groups. Due to financial constraints, no sMRI and DTI sequences will be performed at the second MRI visit. All participants will complete the same fMRI tasks collected during the first MRI visit (e.g., implicit facial expression recognition, emotional go/no go, encoding and retrieval, and resting state tasks). In line with procedures undertaken at the first scan, STAI measures will be obtained prior to scanning whereas SMFQ and Bond VAS measures will be obtained after the scan.

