#### *Longitudinal data analysis plan*

For the fMRI datasets collected at baseline and 24 weeks, we will fit a balanced, mixed effects 2 × 2 (group × time) analysis of variance (ANOVA) model to the brain activation data acquired on patients treated with CBT and healthy adolescents. A significant group × time interaction will identify the effect of CBT, for which appropriate post-hoc tests will be performed. Nonparametric statistical methods of inference correcting for multiple comparisons will be applied to statistically evaluate the main effects of group and time point, and any group × time interaction [50-52].

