## Discussion

An important challenge to adolescent mental health services is the provision of appropriate and effective treatment to adolescents in need at the earliest possible point in time. To overcome this challenge, accuracy in both diagnostic assessment and prognostic evaluation of patients are critical, but as yet clinicians possess no objective tools for either. Diagnostic assessments rely on subjective retrospective information transmission from patient and/or parent to clinician whereas potential prognostic indicators of treatment outcome, such as depressive symptom severity or suicidal tendencies, are poor [43]. Therefore the overall aim of MR-IMPACT is to identify and evaluate objective neurobiological markers of depressive illness in adolescence and prognostic indicators of recovery following psychological treatment for depression.

Neural markers of depression in adolescence will be characterized by comparing structural and functional differences in patients with MDD prior to treatment against a group of healthy adolescent participants matched for demographic characteristics such as age, sex and IQ. Treatment-related changes will be identified by measuring changes in brain functional activation and connectivity prior to treatment and following at least six attended sessions of CBT. A placebo-controlled trial would have been an optimal method for assessing treatment-related changes, but impossible due to ethical constraints. Therefore, changes in brain function in healthy adolescents will also be measured at a second time point matched in length to that of the depressed group to ensure that functional changes indicative of adolescent development are not misidentified as changes related to CBT treatment.

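### The group × time interaction between CBT patients and healthy adolescents is read as the effect of CBT, but it also contains recovery, fluoxetine, non-specific care and selection by attendance

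*Protocol article*

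**What the plan says.** The Longitudinal data analysis plan fits a 2 × 2 (group × time) mixed-effects ANOVA to "brain activation data acquired on patients treated with CBT and healthy adolescents". It then gives the rule of interpretation: "A significant group × time interaction will identify the effect of CBT". Inference is non-parametric and corrected for multiple comparisons.

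Under Follow-up assessment, the only patients rescanned are in the CBT arm, subject to attendance. The rule reads, in part: "have completed a minimum of 6 out of a maximum of 20 offered CBT therapy sessions will be invited back for a second MRI visit". For the comparison group, "All healthy comparison participants will be invited back for a second MRI visit at least 24 weeks from their first scan date". The randomised STPP and SCC arms have no second scan.

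On medication, the Study overview says that "patients allocated to any treatment arm may also be prescribed up to 50 mg of Fluoxetine for symptom reduction in the presenting episode". Under Study participants, patients already on antidepressants are eligible.

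The Discussion concedes: "A placebo-controlled trial would have been an optimal method for assessing treatment-related changes, but impossible due to ethical constraints". It then gives the healthy group one task, which is to keep adolescent development from being mistaken for change due to CBT. The third aim also speaks of identifying treatment-related changes through the healthy comparison group.

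**The concern.** A difference in change between two groups can be attributed to treatment only if the groups would have changed alike without it. Depressed patients and healthy adolescents would not be expected to. Patients enter in a current episode with an MFQ score of 27 or more, and some will improve over 24 weeks whatever they receive. Some may start or change fluoxetine between scans. All receive contact and care beyond the specific content of CBT. Only those who attend enough sessions are rescanned. None of this applies to the healthy group.

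At stake is the third of the three stated objectives. Under the rule as written, any significant interaction would be reported as a neural effect of CBT. A larger sample would make a significant result more likely without making the attribution sounder.

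**Working it through.** **1. What the contrast removes and what it leaves.** The interaction estimates (mean change in rescanned CBT patients) − (mean change in healthy adolescents).

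| Source of change | In patients | In controls | Left in the interaction? |
|---|---|---|---|
| Adolescent development | yes | yes | no, if equal in both groups |
| Repeat scanning | yes | yes | no, if equal in both groups |
| CBT-specific effect | yes | no | yes |
| Natural recovery | yes | no | yes |
| Fluoxetine started or changed between scans | some | no | yes |
| Non-specific care | yes | no | yes |
| Selection on at least 6 sessions | yes | no | yes |

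One estimate carries five components that occur only in patients, and the planned model has no term that separates them.

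**2. Can size tell CBT from medication?** No. The Sample size section takes an antidepressant effect on left amygdala activation, d = 1.02, and assumes a similar effect for CBT. On the plan's own assumption, the two would look alike in this contrast.

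**3. The plan's own sample size.** Inputs from that section are d = 1.02, 80% power and 5% error (two-sided assumed).

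n per group = 2 × [(1.960 + 0.842) / 1.02]² = 15.09, or 30.2 in total.

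This agrees with the stated minimum of 30 if that is a total over both groups; the article does not say whether it is. The arithmetic is not in dispute. The question is what the contrast measures.

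**4. Illustration of the consequence.** Set the CBT effect to zero and let g be the non-CBT change in patients, in SDs of the change score. The documents give no value for g, so the values below are assumptions. The 2 × 2 interaction is a two-sample t-test on change scores. Group sizes are 32 patients (40 less the 20% attrition in the Sample size section) and 40 controls, so df = 32 + 40 − 2 = 70.

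Non-centrality = g / √(1/32 + 1/40) = g / 0.2372.

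| g (assumed) | Non-centrality | P(significant), two-sided 5% | P(significant), two-sided 0.1% |
|---|---|---|---|
| 0 | 0 | 5% | 0.1% |
| 0.3 | 1.26 | 24% | 2% |
| 0.5 | 2.11 | 55% | 10% |
| 0.8 | 3.37 | 91% | 48% |

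The 5% column describes one uncorrected test, which matches the amygdala calculation. The 0.1% column borrows the whole-brain threshold that the Sample size section uses for the predictor analysis. It is a rough stand-in for the planned correction in the longitudinal analysis, whose exact threshold the article does not give.

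**The case against.** **The limitation is partly acknowledged.** The Discussion says that a placebo control would have been best and describes the healthy group as a control for development. This stands as an explanation of the design. It does not qualify the rule of interpretation, and the limitations paragraph discusses a different problem (separating illness markers from general non-response to treatment). Natural recovery and fluoxetine are not named there.

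**The size of the bias is unknown.** This stands. A reader might infer that a significant interaction is to be expected even if CBT does nothing, since the background reports a trial that "noted that CBT alone was not superior to placebo in effecting remission by 12 weeks". The documents do not support that step. The evidence concerns clinical remission, not change in brain activation. The one recovery figure, 50% remission by 2 years in first-episode clinic cases, is not stated to come from untreated patients.

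**Medication may explain little.** A shift of 1.02 SD would need every CBT patient to gain the full antidepressant effect between scans, and patients already medicated at baseline would show less new drug effect. If a quarter gained it (an assumption), the mean shift is 0.25 × 1.02 = 0.255 SD. The probability of significance is then about 19% at 5%, ignoring added variance. That is smaller, but still not the CBT effect.

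**Regression to the mean is indirect.** This also stands. Entry is on diagnosis and MFQ score, so it reaches activation only as far as activation follows symptoms. The point does not rest on it.

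**Rescanning another arm.** A reader might infer that second scans in the STPP or SCC arm would isolate CBT. Both are active treatments, so the result would be CBT relative to that arm. The 6-session minimum would also weaken the randomised comparison.

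**Conclusion.** The concern holds for the interpretation, not for the model or the sample size. The sentence in the Longitudinal data analysis plan claims more than the contrast can deliver, because the interaction mixes any CBT effect with other changes that occur only in patients. This follows from who is rescanned and what treatment is allowed, and needs no numerical assumption.

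The supportable statement is that the interaction may be significant without a CBT-specific effect, with a probability that the documents do not fix. The 24%, 55% and 91% illustrate assumed shifts of 0.3, 0.5 and 0.8 SD in one test at 5% with 32 versus 40. With multiplicity correction they are lower. A reader might call them false-positive rates, but that would confuse confounding with type I error: the test correctly detects a real difference in change, and the mistake lies in naming its cause.

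**What to change.** 1. In the Longitudinal data analysis plan, replace the sentence with: *A significant group × time interaction identifies change in CBT-treated patients beyond that in healthy adolescents; it does not by itself identify an effect of CBT.*
2. Align the third aim, the paragraph on CBT-related change in the Sample size section, and the treatment-related wording in the Discussion.
3. Name natural recovery, fluoxetine and selection on at least 6 sessions in the limitations paragraph.
4. Report the interaction by fluoxetine use, including use started or changed between scans, as a descriptive sensitivity analysis. Report the association between neural change and symptom change beside it. Neither result makes the contrast causal: fluoxetine use is not randomised and may depend on response.

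The cost is some rewording and two analyses, with no extra scans. The claim becomes weaker, and with about 32 rescanned patients the fluoxetine subgroups will be small and imprecise.

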## Discussion

An important challenge to adolescent mental health services is the provision of appropriate and effective treatment to adolescents in need at the earliest possible point in time. To overcome this challenge, accuracy in both diagnostic assessment and prognostic evaluation of patients are critical, but as yet clinicians possess no objective tools for either. Diagnostic assessments rely on subjective retrospective information transmission from patient and/or parent to clinician whereas potential prognostic indicators of treatment outcome, such as depressive symptom severity or suicidal tendencies, are poor [43]. Therefore the overall aim of MR-IMPACT is to identify and evaluate objective neurobiological markers of depressive illness in adolescence and prognostic indicators of recovery following psychological treatment for depression.

Neural markers of depression in adolescence will be characterized by comparing structural and functional differences in patients with MDD prior to treatment against a group of healthy adolescent participants matched for demographic characteristics such as age, sex and IQ. Treatment-related changes will be identified by measuring changes in brain functional activation and connectivity prior to treatment and following at least six attended sessions of CBT. A placebo-controlled trial would have been an optimal method for assessing treatment-related changes, but impossible due to ethical constraints. Therefore, changes in brain function in healthy adolescents will also be measured at a second time point matched in length to that of the depressed group to ensure that functional changes indicative of adolescent development are not misidentified as changes related to CBT treatment.

Short, medium, and long-term predictors of response to treatment by CBT, STPP, and SCC will be identified by relating the extent and rate of improvement in depressive symptoms with pre-treatment measures of brain structure, functional activity and connectivity. To comprehensively test the relationship between structural and functional brain measures and the clinical phenotypes of the depressions we will also perform multivariate analyses focusing on neural systems implicated in adult MDD and on the fronto-limbic system in particular. The longer-term aim of MR-IMPACT, IMPACT, and other adjunct IMPACT studies includes whether relapse and recurrence of depression can be successfully predicted using neurobiological, behavioural, environmental, and genetic indices.

Despite the aim of differentiating state from trait markers of depressive illnesses in adolescence and predictors treatment response, our study is not without limitations. One limitation, common to all longitudinal treatment studies, includes an inability to disaggregate neural markers of illness and neural indicators of treatment-general non-response (i.e., refractory depression). While the simple comparison of treatment responders with treatment non-responders would indicate regions involved in treatment-specific response, the possibility remains that patients would have responded to alternative treatment strategies had they been provided. One way we could have examined neural markers of illness would have been to include within the longitudinal design a group of currently healthy adolescents with a predisposition for developing MDD. However, in order to achieve sufficient statistical power to ensure reliable and reproducible effects, this would have necessitated the initial recruitment of a much larger sample of adolescents than was realistically feasible and so we opted for the current design. Bearing this limitation in mind, we hope the study results will assist in the provision of more targeted treatment strategies to adolescent patients with MDD.

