### Aims

Neuroimaging examinations of adolescents with MDD provide an opportunity to reveal and differentiate pathophysiological and therapeutic neural structure and function between first episode sporadic as well as at risk recurrent forms of this disorder. Using a repeated-measures design in selected cases that have completed psychological treatment provides a longitudinal neuroimaging investigation of therapeutic effects that have the added potential of revealing neural sites that constitute state or trait markers of illness and treatment insensitivity.

MR-IMPACT will therefore examine neural markers of moderate to severe unipolar depression in adolescence and neurobiological predictors of recovery from depression. Specific objectives of MR-IMPACT are as follows:

• To define the profile of brain structural and functional differences in adolescent patients with depression at baseline compared to a group of healthy adolescent participants.

• To assess baseline measurements of brain structure, functional activation and connectivity, focusing on neural systems implicated in adult MDD (ACC and other fronto-limbic components) as predictors of symptomatic response to each of the three types of psychological treatments in the short-to-medium term (up to 86 weeks after the start of treatment).

• To measure changes in brain functional activation and connectivity before and after a course of CBT and development-related changes in brain function measured in a comparison group of healthy participants to permit identification of treatment-related changes in brain function.

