### Study participants

The patient population will be recruited from a larger cohort of young people with depression who have agreed to take part in the IMPACT trial. All eligible and interested patients residing in London or Cambridgeshire will be invited to take part in MR-IMPACT, with enrolment targeted to reach 120 adolescents (male and female) aged 11 through 17 years who meet Diagnostic and Statistical Manual of Mental Disorders (DSM-IV) criteria for moderate to severe unipolar depression. Patients with chronic or recurrent MDD are also included, as are patients already taking antidepressant medication. A detailed list of the study exclusion criteria is provided below.

All patients will be provided an MR-IMPACT study information leaflet and will provide verbal consent to IMPACT research assistants to be contacted by telephone by an MR-IMPACT researcher a minimum of 48 hours later for potential participation in the MR-IMPACT study. Patients will be contacted to assess interest in and eligibility for the magnetic resonance imaging (MRI) scan. Patients with MRI contraindication will be ineligible and therefore excluded from the study at this point. For eligible patients, if the patient so chooses, one adult (typically a parent) may accompany the adolescent patient into the scanner suite. For the patients requesting this option, the identified adult will be screened over the telephone for MRI contraindications. Eligible patients will be scheduled for an MRI appointment where they are remunerated £30 for their time and inconvenience. Any fees incurred for travel to and from the MRI appointment will be reimbursed to the adult accompanying the patient.

A group of healthy control young persons matched for age, sex, intelligence quotient (IQ) and handedness will be recruited into the study for comparison. A letter will first be posted to all families with healthy adolescents who had participated in a previous study (i.e. the ROOTS study) [32]. The letter will describe the MR-IMPACT study and the current recruitment of siblings of ROOTS participants aged between 11 and 17 years, and request that interested families contact a member of the MR-IMPACT team to discuss participation and arrange a home visit. If needed, additional healthy control adolescents will be recruited from local schools within Cambridgeshire.

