### Inclusion criteria

1. Aged 11 through 17 years.

2. Current DSM-IV unipolar MDD diagnoses with moderate to severe impairment determined by child and parent interviews using the K-SADS-PL.

3. Score of 27 or more on the MFQ.

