### Sample size and power calculations

To effectively test the presence of a relationship between pre-treatment imaging markers and post-treatment symptomatic response the study sample size will need to be large enough to overcome the neuroimaging problem of multiple comparisons across the ~300,000 intra-cerebral image voxels and also account for participant attrition. The attrition rate observed during a similar trial (i.e., Adolescent Depression Antidepressants and Psychotherapy Trial [ADAPT]) with a 28-week follow-up period was just 2% [43]. Allowing for an even greater attrition rate of 20% on a pre-treatment sample size of 40 patients per treatment arm, it follows that 32 patients will be available for post-treatment scans. Assuming an effect size of the same size as that observed in a previous study of adults with MDD (R ≥ 0.76 for grey matter volume [GMV] and symptom response in ACC) [8] and a conservative two-tailed probability of p <0.001 to control for multiple comparisons in a whole brain analysis of imaging data, and at least 32 patients completing post-treatment scans, the power to detect a true effect will be at least 95%. Thus with pre-treatment imaging data from 40 patients per treatment arm, the study is strongly powered to assess imaging predictors of recovery following treatment for MDD.

To detect CBT-related changes in brain function, a previous fMRI study of adult MDD [9] and a pilot study examining components of variance in a facial emotion perception task [44] are used to inform calculations of statistical power. Activation of the left amygdala by facial emotion processing showed an effect of antidepressant treatment of d = 1.02 [9]. A similar effect size of CBT will be assumed for the current study, with empirical estimates of between-subject and between-session variance in amygdala response [44] suggesting that a minimum power of 80% will be needed for detection of a true treatment effect. Considered together with a false positive rate of 5%, a minimum of 30 participants will be needed for the detection of CBT-related changes in brain function. The effects obtained in 40 patients in the CBT arm, compared to 40 healthy adolescents, should therefore be sufficiently powerful in size to detect therapeutic changes in amygdala activation equivalent to that observed from antidepressant medication treatment studies of adult patients with MDD.

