#### *sMRI data analysis plan*

Whole brain, multi-channel segmentation [45] and voxel-based morphometry [46] will be used to generate GMV maps from each baseline scan for co-registration into Montreal Neurological Institute (MNI) standard space [47]. Whole brain voxel-based morphometry will first be used to assess the presence of pre-treatment anatomical differences between patients and controls and to explore regions where variation in grey or white matter significantly predict treatment-specific or treatment-general responses [8]. The multivariate technique of partial least squares [48] will also be used to identify patterns of grey matter variation that optimally correlate with treatment response. In an effort to test our hypotheses comprehensively, we will also use the MNI template [49] to anatomically parcellate a priori regions of interest including, but not limited to, subgenual, pregenual and dorsal ACC, amygdala, hippocampus, and prefrontal cortex, where the presence of both group differences in GMV and associations with treatment-specific symptom reductions will be assessed. Non-parametric statistical methods with correction for multiple comparisons [50-52] will be used.

With regard to the DTI dataset, fractional anisotropy and mean diffusivity maps will be created using the Functional Magnetic Resonance Imaging of the Brain (FMRIB) diffusion toolbox in FMRIB Software Library (FSL) [53] by estimating diffusion tensors at each intracerebral voxel prior to using a b = 0 image for mapping into MNI standard space. As with the sMRI data, between-group differences and predictors of treatment response in fractional anisotropy and diffusivity measures will be identified across the whole brain and in a priori regions of interest. For further exploration of group differences and associations with treatment outcome, anatomical connections between frontal and limbic cortex will be measured using probabilistic tractography [54-56].

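### A responder contrast or a within-arm association cannot show treatment-specific prediction, and the article names no comparison of marker effects between the randomised arms

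*Protocol article*

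**What the plan says.** One of the three objectives under Aims is to assess baseline imaging measures "as predictors of symptomatic response to each of the three types of psychological treatments in the short-to-medium term". Under Study overview, the patients "have been randomly allocated to one of three forms of talking therapy" (STPP, SCC or CBT). Study participants sets the size, "with enrolment targeted to reach 120 adolescents (male and female) aged 11 through 17 years", which is 40 per arm.

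The sMRI data analysis plan names both treatment-specific and treatment-general response as targets. For the a priori regions it says that "associations with treatment-specific symptom reductions will be assessed". The fMRI data analysis plan takes the same approach. The Discussion describes the prediction work as "relating the extent and rate of improvement in depressive symptoms with pre-treatment measures" of brain structure, activity and connectivity. Its limitations paragraph then states that "the simple comparison of treatment responders with treatment non-responders would indicate regions involved in treatment-specific response".

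The one power calculation for prediction is a single correlation in one arm. It concludes that "with pre-treatment imaging data from 40 patients per treatment arm, the study is strongly powered" to assess imaging predictors of recovery. The only interaction named in the article is group by time, for CBT patients against healthy adolescents (Longitudinal data analysis plan).

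**The concern.** Comparing responders with non-responders, or correlating a marker with improvement inside one arm, shows that the marker goes with improvement. It does not show that the therapy matters to that link. A marker of generally good prognosis produces the same finding under CBT, STPP and SCC. To call a marker treatment-specific, one needs evidence that its effect differs between therapies. The randomised arms supply the right comparison, but the article does not name it.

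The study hopes to help match patients to therapies. A general prognostic marker labelled as specific to one therapy would point to a choice between therapies that the data do not support. The likely route is a marker that passes the threshold in one arm and misses it in another, which happens often by chance when the true effect is the same in all arms.

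**Working it through.** **Inputs from Sample size and power calculations:** 40 patients per arm, 20% attrition, R = 0.76, two-tailed p < 0.001, stated power at least 95%. Patients remaining per arm: 40 × 0.8 = 32. The critical value is z = 3.29. Correlations other than 0.76 are assumptions, shown as a range.

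**Step 1. The plan's own figure.** By Fisher z, the power for one correlation is Φ(atanh(r)·√(n−3) − 3.29). For r = 0.76 and n = 32, atanh(0.76) = 0.996 and √29 = 5.385. The product is 5.36, and Φ(5.36 − 3.29) = Φ(2.07) = 98.1%. Simulating the t test of r (100,000 runs) also gives 98.1%. The stated figure is correct for an association within one arm.

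**Step 2. The same marker effect in all three arms.** Let p be the per-arm power from step 1. The arms contain different patients, so the chance of significance in one or two arms but not all three is 1 − p³ − (1−p)³.

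| Common true r | Per-arm power | Significant in some but not all arms |
|---|---|---|
| 0.3 | 5.2% | 15% |
| 0.4 | 15.6% | 40% |
| 0.5 | 37.0% | 70% |
| 0.6 | 67.1% | 66% |
| 0.7 | 91.6% | 23% |
| 0.76 | 98.1% | 6% |

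For r = 0.5: 1 − 0.370³ − 0.630³ = 1 − 0.051 − 0.250 = 0.70. In every row the marker is purely prognostic, so a pattern of mixed significance says nothing about specificity.

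**Step 3. Power for a difference between two arms.** The standard error of the difference of two Fisher z values is √(1/29 + 1/29) = 0.263.

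- 0.76 versus 0: 0.996/0.263 = 3.79, and Φ(3.79 − 3.29) = 69%.
- 0.76 versus 0.38: (0.996 − 0.400)/0.263 = 2.27, and Φ(2.27 − 3.29) = 15%.
- By the same formula, 0.76 versus 0.2 gives 39%, versus 0.3 gives 25%, and versus 0.5 gives 6%.
- For 95% power at p < 0.001, about 53 patients per arm are needed for 0.76 versus 0, and 107 for 0.76 versus 0.3.
- At a threshold of 0.05, as might suit one pre-named region, 32 per arm give 97% against 0, 74% against 0.3 and 40% against 0.5.

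A model interaction compares slopes, not correlations. The two agree when the standard deviations are equal across arms, so these figures are a guide to scale.

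**Step 4. The treatment-general question.** Pooling the arms gives 3 × 32 = 96 patients. The correlation detectable with 80% power at p < 0.001 falls from 0.65 (n = 32) to 0.40 (n = 96).

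**The case against.** Several points on the other side have force.

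The sentence about responders stands in a limitations paragraph. It goes on to allow that patients might have responded to a different therapy, and the sentence before it admits that illness markers cannot be told apart from markers of general non-response. The sMRI plan also lists treatment-general response, so the authors know the distinction. These concessions mean one cannot say that general markers *will* be reported as specific. They do not withdraw the claim that the contrast indicates treatment-specific regions, and that claim is wrong as it stands.

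Separate testing by arm is inferred from the objective and the per-arm power calculation; the article does not state it as the only analysis. A fuller plan may contain an interaction model. If so, the Discussion sentence would conflict with it and still need correcting.

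The power section claims power for predictors of recovery and never for specificity, so its figure is not an error. The request is only to say what it covers. The 70% in step 2 is the highest value in the table; at the article's own planning effect it is 6%. No passage adopts a rule that significance in some arms means specificity.

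A reader might also infer that symptom reduction is analysed without baseline adjustment and that, because entry requires a "Score of 27 or more on the MFQ", regression to the mean would create false predictors. The document does not support this. It neither states nor excludes baseline adjustment, which an article may leave to the full plan. The effect would also be common to all arms, so it could not by itself create arm-specific prediction. It would be small too. Assume a marker tied only to baseline score (correlation c from 0.2 to 0.5), a baseline to follow-up correlation ρ from 0.2 to 0.5, and equal standard deviations. The induced correlation with change, c(1−ρ)/√(2(1−ρ)), is then 0.10 to 0.32. With 32 patients it passes p < 0.001 in 0.3% to 6% of cases.

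**Conclusion.** The point holds in a limited form. The Discussion states an inference that its comparison cannot support, the analysis plans use the term treatment-specific, and the article names no between-arm comparison of marker effects although randomisation allows one.

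The risk of being misled is greatest at intermediate correlations: 40% to 70% for a common r of 0.4 to 0.6, and much lower at 0.3 or at 0.76. These chances assume equal true correlations in all arms, 32 patients per arm and the planned threshold. The stated power is right for within-arm association and does not carry over to specificity, where it is about 69% in the favourable case of 0.76 versus 0 and falls quickly as the other arm's correlation rises.

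The documents do not show that false claims of specificity are certain, that change scores go unadjusted, or that the power calculation is wrong.

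**What to change.** 1. In the Discussion, reword the responder sentence so that the regions found are described as associated with response within that treatment.
2. In the sMRI and fMRI analysis plans, reserve the term treatment-specific for a marker-by-arm interaction. Fit one model to all randomised MR-IMPACT patients: follow-up symptom score on baseline score, arm, marker and marker × arm. Take treatment-general prediction from the pooled marker effect. Baseline score is there as a good-practice covariate, not as the repair of a shown error.
3. In Sample size and power calculations, add that the figure of at least 95% covers association within one arm only, and give the power for a between-arm difference (about 69% for 0.76 versus 0 and 15% for 0.76 versus 0.38, at p < 0.001).

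The cost is wording and one model specification. Arm, symptom scores and baseline imaging are already part of the study, so no new data are needed. The downside is that the lower power for treatment-specific claims becomes visible.
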